#### Assessment of recurrence

In patients showing signs of local recurrence during follow-up, MRI, CT, PET-CT or ultrasound-guided fine-needle aspiration cytology (US-FNAC) should be performed to confirm recurrence, as necessary. The planning CT and diagnostic imaging modalities will be compared side-by-side to determine the exact site of recurrence and its relative location to the ISI region.

#### Assessment of toxicity and QoL

Acute treatment-related toxicities will be graded using the National Cancer Institute Common Terminology Criteria for Adverse Events (CTCAE) version 5.0. The Radiation Therapy Oncology Group (RTOG) and European Organization for Research and Treatment of Cancer (EORTC) late radiation morbidity scoring schemes will be used to assess late radiation toxic effects. The EORTC QLQ-C30 and EORTC QLQ-H&N35 questionnaires will be applied to evaluate the general QoL. The Groningen Radiation Therapy Induced Xerostomia questionnaire (GRIX) will be used to assess the QoL associated with serostomia. The MD Anderson Dysphagia Inventory (MDADI) composite score and Swallowing Quality of Life Questionnaire (SWAL-QoL) will be used to evaluate swallowing capacity and dysphagia-related QoL.

#### Sample size calculation

The primary endpoint is RRFS. Based on previous reports, the 3-year failure free regional control rate was assumed to be 96% in both groups [23]. According to expert consensus, data from institutional experiences, and published literature, a 6% difference was set as the noninferiority margin [3, 7, 24]. To obtain a power of 85% and a one-sided α value of 2.5%, a total of 414 patients would be enrolled with a dropout or loss of follow-up rate of 5%.

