### Randomization

An eligibility checklist and patient consent must be completed and obtained before randomization. Eligible patients will be allocated randomly to the ISI and ERI groups on a 1:1 basis using a computer-generated randomization scheme with a block size of four. Randomization will be stratified by institution scale (large vs small) and N stage (N0 vs N1 vs N2).

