### Statistical analysis

The case distribution between the ISI and ERI groups in each center will be described. Compliance will be assessed according to the case report form to compare implementation between the two groups. Total drop-out rates and adverse event drop-out rates will be compared between the two groups using Fisher’s exact test. Baseline comparisons will be performed by using *t*-tests or non-parametric tests for continuous data. Chi-square test will be used to compare categorical data. Both intention-to-treat (ITT) and per-protocol (PP) analysis will be used to assess the efficacy of ISI. Safety analysis will be performed in the safety population. Time-to-event data will be censored in the absence of observations of regional failure at the date of last follow-up or loss to follow-up. The Kaplan–Meier method will be used to estimate the survival rates. Differences between treatment groups will be assessed using log-rank tests. Interaction analysis for RRFS will be undertaken to assess whether differential effects were present between ISI and ERI in predefined subgroups. Adverse events will be listed and analyzed using the chi-square test or Fisher’s exact test. Serious adverse events should be listed in detail and compared between groups. The principal investigator and the protocol committee will perform the analysis. A Data Monitoring Committee (DMC) will be set up to oversee the trial and to decide whether the trial should be stopped.

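### 414 patients follows from the unpooled normal approximation, but with about 8 expected failures per arm the usual difference-scale methods do not deliver one-sided 2.5% error and 85% power together; methods that hold 2.5% give about 80% power

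*Protocol article*

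**What the plan says.** All the design inputs are in the protocol article.

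- Sample size calculation: "the 3-year failure free regional control rate was assumed to be 96% in both groups", and "a 6% difference was set as the noninferiority margin".
- The same section then states: "To obtain a power of 85% and a one-sided α value of 2.5%, a total of 414 patients would be enrolled". This total allows for 5% dropout or loss to follow-up. No formula is named.
- Randomization: "Eligible patients will be allocated randomly to the ISI and ERI groups on a 1:1 basis", so 207 per arm.
- Statistical analysis: "The Kaplan–Meier method will be used to estimate the survival rates". Group differences are to be assessed with log-rank tests.

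The article does not say which interval or test will be set against the margin. That may be in an analysis plan that is not shown, and its absence is not the point here.

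**The concern.** The section commits to one pair of operating characteristics, a 2.5% one-sided error and 85% power, at one sample size. At a 96% success rate the information lies in a handful of failures, about 8 per arm. Normal-approximation intervals for a difference tend to be too narrow there.

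If so, one of two things follows. Either the decision rule accepts involved site irradiation more often than 2.5% of the time when it is truly 6 points worse, or a rule that keeps 2.5% has less than 85% power. In a de-escalation trial the first is the more harmful, because the error favours the reduced treatment.

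**Working it through.** **Inputs** (Sample size calculation; Randomization): success 0.96 in both arms; margin 0.06, so the design null is 0.90 versus 0.96; one-sided alpha 0.025 (z = 1.960); power 0.85 (z = 1.036); 1:1 allocation; 414 enrolled; 5% loss.

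**1. Reproduce 414.** Unpooled normal formula:

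n per arm = (1.960 + 1.036)² × 2 × 0.96 × 0.04 / 0.06² = 191.5, so 192 per arm and 384 in total.

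384 / 0.95 = 404.2. Depending on rounding this is 404 to 406 enrolled. The stated 414 is about 2% higher. Other formulas do not fit the stated inputs: the Farrington-Manning score formula needs 234 per arm (about 493 enrolled), and a complementary log-log scale needs about 500 per arm. The unpooled formula is therefore the likely source, by inference.

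**2. Evaluable patients and events.** 414 / 2 = 207 per arm; 207 × 0.95 = 196.7, so 196-197 evaluable. Expected failures at 4%: 0.04 × 197 = 7.9 per arm.

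**3. Exact operating characteristics.** Every pair of binomial outcomes was enumerated. Non-inferiority is declared when the lower limit of the two-sided 95% interval for the difference (ISI minus ERI) lies above −6 points. Error is taken at 90% versus 96%, power at 96% versus 96%.

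| Method | Error, 196 / 197 per arm | Power, 196 / 197 per arm | Error, 207 (no loss) | Power, 207 (no loss) |
|---|---|---|---|---|
| Wald (unpooled) | 3.27% / 3.21% | 86.0% / 85.8% | 3.02% | 86.6% |
| Farrington-Manning score | 2.28% / 2.30% | 78.9% / 80.1% | 2.27% | 82.1% |
| Newcombe | 2.36% / 2.30% | 80.3% / 81.0% | 2.42% | 82.8% |

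The relative excess for Wald is (3.27 − 2.5)/2.5 = 31%, or (3.21 − 2.5)/2.5 = 28%.

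**4. Same check with Kaplan-Meier estimates.** Simulation with 207 enrolled per arm and 5% loss by 3 years (40,000 runs for error), done twice independently:

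- Wald interval with Greenwood variance: error 3.0-3.2%, power about 86%.
- Log-log limits combined for the difference: error 2.1-2.2%, power about 80%.

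The split is therefore not an artefact of treating the endpoint as binomial.

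**5. Sensitivity.**

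- If failure in the ERI arm is 2.5% (null 91.5% versus 97.5%), the Wald error at 196-197 per arm is about 3.6%. The Background section reports 5-year RRFS of 97.6% and 97.5% for N0 and N1, but 94.6% for N2, so the mix could move the rate either way.
- A Wald test with its critical value raised so that error is 2.5% at the design null (about 2.06-2.07 instead of 1.96) has 83.0-83.8% power at 196-197 per arm, and 85.1% at 207 with no loss. It does not control error over the rest of the null.
- A hazard-ratio test with the margin converted to ln 0.90 / ln 0.96 = 2.58 has about 47% power on about 16 events.
- Score and Newcombe reach about 85% power at about 220-225 evaluable per arm, roughly 464-474 enrolled.

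**The case against.** **It is only the nominal-versus-exact gap.** Sample-size statements are conventionally nominal, and 414 reproduces under a standard formula. This stands. A reader might infer from the figures above that 414 was miscalculated; the document does not support that.

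**The defect depends on a test that the article does not name.** If the analysis plan uses a score or log-log interval, the excess error disappears; if it uses Wald, the power shortfall disappears. This stands as a limit. A reader might infer that the trial will run at 3.2-3.3% error, but the article does not say that a Wald interval will decide the result, and a planning formula is not an analysis. It does not rescue the stated pair, however: each usual difference-scale choice loses either the 2.5% or the 85%.

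**The 79-81% does not cover every method that holds 2.5%.** Correct. It applies to score, Newcombe and log-log intervals with the planned 5% loss. With no loss, score and Newcombe reach 82-83%, and the recalibrated Wald test gives about 83-84% at 196-197 per arm.

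**The shortfall is small against uncertainty in the 96%.** At 197 per arm, Newcombe power is 81.0% at 96% control, 84.9% at 96.5% and 88.6% at 97%; score gives 80.1%, 83.6% and 87.2%. So half a point in the assumed rate matters about as much as the choice of interval, and 80% is still a conventional level. This argues for keeping 414 patients. It does not make the pair true at the 96% that the section assumes.

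**Conclusion.** The point holds in a limited form. The 414 is correctly derived from the unpooled normal approximation, with a small excess. The 2.5% error and 85% power attached to it are nominal, and none of the usual difference-scale methods checked achieves both at this size.

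The size of the gap at the design rates and 5% loss is either 0.7-0.8 points of excess one-sided error (3.2-3.3% against 2.5%) with power kept at about 86%, or 4-6 points less power (79-81% against 85%) with error kept at 2.5%.

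This rests on 96% control in both arms, a null of 90% versus 96%, 196-197 evaluable per arm, a decision made on the difference scale, and the inference about which formula was used. The article does not show which side of the trade-off the trial will fall on.

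**What to change.** Keep 414 patients and make two changes.

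1. Base the non-inferiority decision on a two-sided 95% interval for the 3-year RRFS difference that holds its level near 96%: a score or Newcombe type interval, or Kaplan-Meier log-log limits combined for the difference. If the analysis plan already specifies such an interval, only the second change is needed.
2. In the sample size section, name the formula behind 414 and restate the power as about 80% (79-81%) at one-sided 2.5% under the chosen interval, with 5% loss.

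The cost is one sentence on method and a slightly less favourable stated power. Keeping 85% instead would mean enrolling roughly 464-474, some 50 to 60 more patients, which the size of the gap does not call for. The article reports recruitment as ongoing, so the change should be made before the primary data are analysed.

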### Statistical analysis

The case distribution between the ISI and ERI groups in each center will be described. Compliance will be assessed according to the case report form to compare implementation between the two groups. Total drop-out rates and adverse event drop-out rates will be compared between the two groups using Fisher’s exact test. Baseline comparisons will be performed by using *t*-tests or non-parametric tests for continuous data. Chi-square test will be used to compare categorical data. Both intention-to-treat (ITT) and per-protocol (PP) analysis will be used to assess the efficacy of ISI. Safety analysis will be performed in the safety population. Time-to-event data will be censored in the absence of observations of regional failure at the date of last follow-up or loss to follow-up. The Kaplan–Meier method will be used to estimate the survival rates. Differences between treatment groups will be assessed using log-rank tests. Interaction analysis for RRFS will be undertaken to assess whether differential effects were present between ISI and ERI in predefined subgroups. Adverse events will be listed and analyzed using the chi-square test or Fisher’s exact test. Serious adverse events should be listed in detail and compared between groups. The principal investigator and the protocol committee will perform the analysis. A Data Monitoring Committee (DMC) will be set up to oversee the trial and to decide whether the trial should be stopped.

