## Methods

### Study design

This study is designed as a multicenter, noninferiority, subject-blinded, randomized, phase III trial. A total of 414 patients harboring stage I-III NPC with LB-LN (detailed definition is presented in “Inclusion criteria” section) from eight tertiary hospitals in China will be randomized (1:1) to the ISI or ERI groups. The flow chart and study design schedule are presented in Fig. 1; Table 1, respectively.

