### Primary endpoint

The 3-year RRFS (Regional-recurrence-free survival, which is measured from the registration to the documented regional recurrence) will be compared between the ISI and ERI groups.

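### The only between-arm efficacy test named is a log-rank test of differences, which does not test the 6-point non-inferiority margin on 3-year RRFS that the 414 patients were sized for

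*Protocol article*

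**What the plan says.** All references are to the Methods of the protocol article.

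- **Study design** declares the objective: "This study is designed as a multicenter, noninferiority, subject-blinded, randomized, phase III trial".
- **Primary endpoint** fixes the time point. It is RRFS at 3 years, which "will be compared between the ISI and ERI groups".
- **Sample size calculation** states that "the 3-year failure free regional control rate was assumed to be 96% in both groups" and that "a 6% difference was set as the noninferiority margin". It gives a one-sided alpha of 2.5%, power of 85%, a total of 414 patients and 5% dropout or loss.
- **Statistical analysis** says that survival rates are estimated by Kaplan-Meier, and then: "Differences between treatment groups will be assessed using log-rank tests". It adds: "Both intention-to-treat (ITT) and per-protocol (PP) analysis will be used to assess the efficacy of ISI".

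The Statistical analysis section does not mention the margin, a confidence interval for the 3-year difference, a shifted null hypothesis or a criterion for declaring non-inferiority. It names no other between-arm test for the time-to-event outcomes.

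**The concern.** The sample size section and the analysis section address different hypotheses. The first asks whether a loss of 6 points or more in 3-year RRFS can be ruled out. The second asks whether the two RRFS curves differ at all. The log-rank test uses the whole curve rather than year 3, and the margin does not enter it.

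The two questions can have different answers. A non-significant log-rank test is compatible with a deficit at or beyond the margin, particularly with few regional failures. A significant one does not by itself rule out non-inferiority.

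The trial's main conclusion is meant to be that ISI is non-inferior to elective region irradiation (ERI). If the named test were all there was, the 2.5% error rate and the 85% power would not belong to the analysis performed, and the published plan would give no criterion for that conclusion.

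**Working it through.** **Inputs.** From Sample size calculation: 96% 3-year control in both arms, 6% margin, one-sided alpha 2.5%, power 85%, 414 patients, 5% dropout. From Randomization: 1:1 allocation, so 207 per arm. Assumptions: the 6% is absolute (96% against 90%), event times are exponential, the log-rank test is two-sided at 5% (no level is stated), and patients are followed to year 3.

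**1. Which test does 414 belong to?** For a non-inferiority comparison of two proportions with no true difference:

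n per arm = [0.96 × 0.04 + 0.96 × 0.04] × (1.960 + 1.036)² / 0.06² = 0.0768 × 8.98 / 0.0036 = 191.5, rounded up to 192.

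The total is 384, and 384 / 0.95 = 404.2, so 405 (406 if rounded per arm). This is about 2% below 414, so the stated figure is reproduced as a margin test on 3-year rates.

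**2. Power of that test at the planned size.** 414 × 0.95 = 393.3, or about 197 evaluable per arm.

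- SE = √(0.0768 / 197) = 0.01974
- Power = Φ(0.06 / 0.01974 − 1.96) = Φ(1.08) = 0.86

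Exact binomial enumeration with a simple Wald interval gives 85.8% power when both arms are at 96%. It gives a 3.2% chance of passing ISI when ISI is exactly at the margin (nominal 2.5%).

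**3. What the log-rank test does in the same trial.** Simulated proportion of trials with a non-significant result, 207 per arm, 5% loss over 3 years:

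| True 3-year RRFS, ISI vs ERI | Log-rank non-significant |
|---|---|
| 92% vs 96% | about 60% |
| 90% vs 96% (at the margin) | about 32% |
| 88% vs 96% (beyond the margin) | about 14% |

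Repeat simulations put the middle row at 32% to 34%; the upper figure is for 197 fully followed patients per arm. An analytic check for 197 per arm:

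- hazard ratio at the margin = ln(0.90) / ln(0.96) = 2.58, with log 0.948
- expected events = 197 × (0.04 + 0.10) = 27.6
- power = Φ(√(27.6 / 4) × 0.948 − 1.96) = Φ(0.53) = 0.70, so 30% non-significant

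**4. How often the two tests disagree (197 per arm, simulated).** At the margin, about 31% of trials have a non-significant log-rank test and fail the margin test. With both arms at 96%, about 2.5% have a significant log-rank test although the margin test is met.

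**5. One concrete result.** Take 16 regional failures of 197 with ISI and 8 of 197 with ERI.

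- Difference in RRFS = 181/197 − 189/197 = −4.1 points
- Lower 95% limit = −8.8 points
- Two-sided p = 0.09 (two-proportion z-test, standing in for the log-rank test)

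There is no significant difference, yet a 6-point loss is not excluded.

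**The case against.** The best reply is that the article already supplies the non-inferiority frame: the design, the 3-year time point, the margin, the one-sided alpha, Kaplan-Meier estimation and both analysis sets. Only the link between them is missing, and a condensed article may leave that to a full protocol or analysis plan that is not shown. The log-rank sentence is also general. It follows a sentence on survival rates in the plural, so it may be aimed partly at overall survival (OS), distant metastasis-free survival (DMFS) and progression-free survival (PFS), for which it is suitable.

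Much of this stands, and it rules out several stronger readings that a reader might infer:

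- **That the log-rank test is declared the primary analysis.** The sentence does not say so. That it covers RRFS is inferred from the absence of any other efficacy test.
- **That a non-significant result will be taken as non-inferiority.** No section states this rule. The 32% is what such a reading would risk, not the error rate of a stated procedure. It also refers to the true difference: an observed deficit of 6 points would usually be significant (20 against 8 failures of 197 is −6.1 points, p = 0.02).
- **That the trial is underpowered for a hazard-ratio margin.** The article proposes no such test.
- **That the power must be restated for a particular interval method.** The article names no interval, and 85% reproduces under the standard formula. The choice of method is a refinement.

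The reply does not remove the point itself. The article is not silent on the test. It names one, and that one does not match the hypothesis used to size the trial. If an analysis plan holds the margin-based analysis, the published sentence still has to be reconciled with it.

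**Conclusion.** The point holds in a limited form. As published, the one between-arm test stated for RRFS does not test the 6-point margin at one-sided 2.5%. A non-significant result from it could not support a non-inferiority claim: it would occur in about 32% of trials with ISI truly at the margin, where a margin-based interval would pass ISI in about 3%. These figures rest on the assumptions listed with the inputs.

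The defect lies in the stated analysis, not in the size of the trial. The 414 patients and the 85% power agree with a margin test on 3-year rates. The documents do not support the conclusion that the investigators intend to declare non-inferiority from a non-significant log-rank test.

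**What to change.** For RRFS, state in Statistical analysis that:

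- the primary analysis is the difference in 3-year Kaplan-Meier RRFS (ISI minus ERI) with a two-sided 95% confidence interval;
- non-inferiority is claimed only if the lower limit is above −6 percentage points;
- this is assessed in both the intention-to-treat and the per-protocol sets.

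Keep the log-rank test as supportive for RRFS and for OS, DMFS and PFS.

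The cost is wording only, with no extra patients, visits or data. The sample size and the stated power stay as they are. The 86% applies to one analysis set; the chance of meeting the criterion in both sets has not been calculated here. The change should be made, or the text reconciled with any existing analysis plan, before outcome data are analysed, because a criterion chosen afterwards would carry little weight.

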### Secondary endpoint

The effects of ISI on 3-year OS (measured from registration to documented death from any cause or last follow-up), distant metastasis-free survival (DMFS, measured from registration to documented distant metastasis or death from any cause), and progression-free survival (PFS, measured from registration to documented locoregional recurrence or distant metastasis or death from any cause); early (from the start of radiotherapy until the 1 month after radiotherapy) and late toxicities; and general and late toxicity-related QoL will be evaluated.

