#### Follow-up

During the treatment course, all enrolled patients will be examined and treatment-related adverse events will be carefully documented weekly. Patients will be followed up at least every three months in the first two years, six months in the third to fifth year, and then yearly. The detailed schedule and examination items are shown in Table 1.

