### Trial status

The Recruitment started in August 2022 and is currently ongoing.

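### Late toxicity is assigned a chi-square or Fisher test with no time horizon, so the comparison, read naturally, would be a crude proportion that does not estimate 3-year toxicity

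*Protocol article*

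**What the plan says.** All references are to the protocol article.

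- **Test.** Statistical analysis names one method for toxicity: "Adverse events will be listed and analyzed using the chi-square test" or Fisher's exact test. It adds "Safety analysis will be performed in the safety population". No time point is attached.
- **Time-to-event methods.** The same section says "The Kaplan–Meier method will be used to estimate the survival rates", and its censoring rule is written for regional failure. Neither is extended to toxicity.
- **Windows.** Secondary endpoint lists "early (from the start of radiotherapy until the 1 month after radiotherapy) and late toxicities". The early window has a start and an end; the late one has no end.
- **Follow-up.** Visits are at least every three months for two years, then every "six months in the third to fifth year, and then yearly". Table 1 schedules toxicity reporting at all of them.
- **Entry.** Trial status says "The Recruitment started in August 2022 and is currently ongoing", so entry is staggered.
- **Loss.** Sample size calculation allows 5% overall, with no rate by arm. Statistical analysis adds that "Total drop-out rates and adverse event drop-out rates will be compared between the two groups".

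**The concern.** A chi-square test on patients with and without an event answers a clear question when everyone is observed over the same closed window. That holds for early toxicity. For late toxicity, a patient lost or dead at 8 months without an event would count the same as one observed free of toxicity for 5 years. The resulting percentage mixes follow-up times that differ by years and belongs to no particular time point.

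The stake is practical. The Abstract and Discussion present lower toxicity and better long-term quality of life, without loss of regional control, as the reason to adopt ISI. If non-inferiority is shown, the case for ISI rests on toxicity and quality of life. The primary endpoint and overall survival are set at 3 years; a late-toxicity figure without a horizon cannot be placed beside them or compared with other trials.

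**Working it through.** **1. The plan's own figure.** The article gives no figure for the toxicity comparison; its only calculation is for the primary endpoint. With 96% in both arms, a 6-point margin, one-sided 2.5% and 85% power:

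n per arm = (1.960 + 1.036)² × 2 × 0.96 × 0.04 / 0.06² = 191.5, so 192 per arm and 384 in total; 384 / 0.95 = 405.

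This is within 3% of the stated 414. I use 414 / 2 = 207 per arm below.

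**2. Dependence on follow-up length.** Assume a constant hazard and a 3-year risk of 30%: h = −ln(0.70)/3 = 0.1189 per year. The proportion with an event by time F is 1 − exp(−hF):

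| Follow-up | 1 year | 2 years | 3 years | 5 years |
|---|---|---|---|---|
| Proportion | 11% | 21% | 30% | 45% |

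**3. What a crude proportion would show.** Assumptions, none from the article: constant hazards; 6% deaths and 5% loss by year 3 in each arm; uniform accrual over 3 years; analysis when the last patient reaches 3 years. Potential follow-up is then uniform from 3 to B = 6 years.

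With loss hazard g = −ln(0.95)/3 = 0.0171, death hazard m = −ln(0.94)/3 = 0.0206 and s = h + g + m:

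P = (h/s) × [1 − (e^(−3s) − e^(−Bs)) / ((B − 3)s)]

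- 30% risk: h = 0.1189, s = 0.1566. P = 0.759 × [1 − (0.6251 − 0.3908)/0.4698] = 0.38.
- 20% risk: h = 0.0744, s = 0.1121. P = 0.664 × [1 − (0.7144 − 0.5104)/0.3363] = 0.26.

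A true 10-point difference appears as about 12 points. By the same formula, 50% vs 37% appears as 60% vs 46%. Changing only the accrual period moves the 30% vs 20% result: 2 years (B = 5) gives 35% vs 24%, and 4 years (B = 7) gives 41% vs 28%.

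**4. Level of the test.** Same assumptions, no true difference, two-sided 5%. Let d be the expected difference in crude proportions produced by unequal loss, and SE = √(2p(1−p)/207) with p the mean proportion. The rejection rate is approximately Φ(d/SE − 1.96) + Φ(−d/SE − 1.96).

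| Loss by year 3 | 30% toxicity | 50% toxicity |
|---|---|---|
| 5% vs 5% | 5.0% | 5.0% |
| 3% vs 7% | 5.6% | 6.2% |
| 0% vs 10% | 8.7% | 12.4% |

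Example, 30% toxicity and 0% vs 10%: crude proportions 0.394 and 0.367, d = 0.027, SE = 0.0477, d/SE = 0.57; 0.082 + 0.006 = 0.087. Simulation agrees with the table to within half a point.

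If everyone is instead followed for exactly 3 years, with 3-year risks from 10% to 50%, the rates are 5.05-5.4% at 3% vs 7% and 5.3-7.4% at 0% vs 10%.

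**5. Power with equal 5% loss.** In simulation under the step 3 assumptions, chi-square against a cause-specific log-rank test gives 75.0% vs 76.7% (30% vs 20%) and 82.0% vs 85.4% (50% vs 37%).

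**The case against.** The strongest reply is that the article never says ever/never. Its sentence would also fit a test of prevalence or cumulative proportion at a fixed visit, and a condensed article may leave the horizon, grade and estimator to the full plan. This stands in part: the crude proportion is the natural reading, not a stated fact. Still, the article does not leave the method open. It names a single test for all adverse events, closes the early window and not the late one, and writes its time-to-event methods only for survival and regional failure.

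A reader might also infer that the plan inflates false positives. The documents do not support that. With equal loss the test holds its level, and no passage predicts unequal loss. Comparing drop-out by arm is a routine check, not a forecast of imbalance. The Abstract calls the trial open-label, but Study design calls it subject-blinded, so little can be drawn from blinding. The 0% vs 10% split is the most unequal one that still averages the planned 5%.

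A time-to-event analysis is no complete protection either. If loss is related to toxicity risk, censoring is informative: with an assumed shared frailty in one arm, the log-rank test's type I error rose to 5.6-6.6% at 5% vs 15% loss, still below that of the crude test. Time to first event also hides resolution, so prevalence at set visits is a legitimate companion.

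**Conclusion.** The point holds for the estimate. On the natural reading, the late-toxicity percentage has no horizon, shifts with accrual speed and analysis date, and does not estimate 3-year toxicity: about 38% vs 26% where the true 3-year risks are 30% vs 20%. This needs no assumption about unequal loss. The size does rest on assumed toxicity risks, constant hazards, mortality, accrual and analysis date, none of which the article gives.

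False-positive inflation is a conditional side point. It is nil with equal loss, small at 3% vs 7% (about 5-6%), and reaches about 8-13% only with a 10-point difference in loss. If loss did differ, the bias would favour the arm that lost more patients. The power gain from a time-to-event analysis is modest, about 2 to 3 points in the base case. The change is worth making for an interpretable estimate.

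**What to change.** In Statistical analysis:

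- Keep chi-square or Fisher's exact test for early toxicity.
- For late toxicity, report by arm the 3-year cumulative incidence of the first late event of a pre-set grade, from a stated time origin, using the Aalen-Johansen estimator with death as a competing event and censoring at the last toxicity assessment. Give the difference with its 95% CI.
- Show loss to follow-up by arm beside it, and keep crude counts as a descriptive table.
- Show prevalence at set visits alongside, because time to first event does not capture resolution.

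If the full plan already fixes a late-toxicity time point, stating it is enough to settle the horizon.

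The cost is a sentence or two and slightly more analysis work; Table 1 already schedules toxicity reporting at every visit. The figures become less directly comparable with published crude rates, which the descriptive table partly offsets.
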